#### Secondary outcomes

The secondary outcomes are as follows:
The response rate assessed by the Brief Psychiatric Rating Scale-18 items (BPRS-18) 3 months after the end of the treatment in patients following the long protocol compared to those following the short protocol (the response being defined as a reduction of 30% on the BPRS).The response rates assessed by the PANSS and the BPRS at different times (2, 4, 6, and 12 months) between both groups.The Hamilton Rating Scale-21 items (HAMD-21) score, the Young Mania Rating Scale (YMRS) score, the Modified Overt Aggression Scale (MOAS) score, the Clinical Global Impression (CGI) score, and the Global Assessment Functioning (GAF) score at baseline and at 2, 4, 6, 9, 12, and 15 months. Changes from baseline will be compared between both groups.The Mini-Mental Status Examination (MMSE), the Subjective Scale to Investigate Cognition in Schizophrenia (SSTICS) [13], the RL/RI-16 test assessing verbal memory [14], the Doors test assessing visual memory [15], the D2 Attention Test [16], and the Copy of the Rey-Osterrieth Complex figure test for the evaluation of visuospatial constructional ability [17] at baseline and at 6 and 15 months. Changes between baseline and 6 months and between baseline and 15 months will be compared between the groups.Plasma clozapine concentration measured at baseline and at 2, 4, 6, 9, 12, and 15 months in order to check patient compliance.

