### Sample size {14}

The aim of this trial is to compare the response rates between short and long ECT protocols. According to the meta-analysis of Lally et al. [7], the proportion of patients with treatment-resistant schizophrenia that responds to ECT augmentation of clozapine was 61.79% (Table 1: 55/89 cases). However, the relapse following ECT cessation is very high: the relapse rate has been estimated at 62.5% by Kho et al. [18]. On the other hand, Braga et al. [19] suggested that ECT were effective as a continuation strategy to prevent relapse after an acute course of ECT. During the 6-month maintenance period, no patient presented with clinically worsening symptoms. From this literature data, we postulate that the responder rates would be 61.79% in the long ECT protocol and 23.25% in the short ECT protocol (62% × (1 − 0.625) = 23.25%). Assuming an alpha risk of 0.05 and a power of 0.80, we estimated the need to include 25 patients per group. To overcome an estimated 20% drop-out, the required number of patients increased to 32 patients per group. As a result, the total number of participants required for the study is 64 patients.

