## Statistical methods

### Statistical methods for primary and secondary outcomes {20a}

Patient characteristics will be described overall and by randomly allocated treatment arm (short or long therapy) using the usual parameters, i.e., mean, standard deviation, median, interquartile range, and range for quantitative characteristics and frequencies for categorical characteristics.

The main outcome (the response rate in the PANSS three months after treatment cessation) being categorical, Pearson’s chi-square test will be used. The same strategy will be applied for the other categorical criteria (secondary outcomes). For the secondary outcomes with quantitative measures, the comparison between both groups will be performed thanks to the repeated measures ANOVA or Mann-Whitney tests based on delta scores (i.e., month 6 minus baseline, month 15 minus baseline), when the assumptions of variance equality and/or normal distribution are violated. If multiple Mann-Whitney tests are performed, Bonferroni adjustment will be applied to compensate for the risk of type 1 errors.

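### Single-step Bonferroni for the secondary rank tests is valid, but Holm's step-down gives the same error control and never rejects less: an optional, mostly small gain

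*Protocol article*

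**What the plan says.** The section on statistical methods for primary and secondary outcomes {20a} sets three rules that matter here.

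- **Primary outcome.** It is tested once: "being categorical, Pearson’s chi-square test will be used". No multiplicity rule applies to it.
- **Quantitative secondary outcomes.** These go to repeated measures ANOVA, with a fallback to "Mann-Whitney tests based on delta scores (i.e., month 6 minus baseline, month 15 minus baseline), when the assumptions of variance equality and/or normal distribution are" not met.
- **Adjustment.** It attaches to the fallback only: "If multiple Mann-Whitney tests are performed, Bonferroni adjustment will be applied to compensate for the risk of type 1 errors".

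The Secondary outcomes section lists the scales. Five are clinical (HAMD-21, YMRS, MOAS, CGI, GAF): "Changes from baseline will be compared between both groups". Six are cognitive (MMSE, SSTICS, RL/RI-16, Doors, D2, Rey figure copy): "Changes between baseline and 6 months and between baseline and 15 months will be compared between the groups".

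The article does not say how many rank tests form one family, and it claims no power for any secondary outcome.

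**The concern.** The article does not leave the adjustment open; it names single-step Bonferroni. Every p-value in the family is then compared with alpha/m, however many of the other tests have already been rejected. Holm relaxes that threshold after each rejection, at no cost in family-wise error and with no added assumption about how the tests are correlated. For deciding which hypotheses to reject, the named method is therefore dominated by one that is equally easy to apply.

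At stake is some power on secondary comparisons when several of them carry real arm differences. The validity of the trial's conclusions is not at stake.

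**Working it through.** **1. The plan's own figure, to see whether the rule touches it.** The Sample size section states: "we postulate that the responder rates would be 61.79% in the long ECT protocol and 23.25% in the short ECT protocol", and "Assuming an alpha risk of 0.05 and a power of 0.80, we estimated the need to include 25 patients per group". With p1 = 0.6179, p2 = 0.2325, mean 0.4252, two-sided alpha 0.05 and power 0.80:

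n = [1.960·√(2·0.4252·0.5748) + 0.8416·√(0.6179·0.3821 + 0.2325·0.7675)]² / (0.3854)²
= (1.370 + 0.542)² / 0.1485 = 24.6, so 25 per group.

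With 20% drop-out, 25/0.8 = 31.25, so 32 per group and 64 in all. This reproduces the article ("To overcome an estimated 20% drop-out, the required number of patients increased to 32 patients per group"). The calculation rests on the single chi-square test, so the rule for the rank tests does not enter it.

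**2. Possible family sizes.** The article fixes none, so these are a range:
- two deltas of one scale: m = 2, Bonferroni threshold 0.05/2 = 0.025
- six cognitive instruments × two deltas: m = 12, threshold 0.05/12 = 0.0042
- eleven scales × two deltas: m = 22, threshold 0.05/22 = 0.0023. This is reached only if every scale falls back to rank tests and all are pooled.

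**3. Why Holm cannot lose.** Order the p-values p(1) ≤ … ≤ p(m). Bonferroni rejects any p ≤ α/m. Holm rejects p(1), p(2), … in turn as long as p(i) ≤ α/(m−i+1), and stops at the first failure.
- Since α/(m−i+1) ≥ α/m, whatever Bonferroni rejects, Holm rejects.
- If m0 hypotheses are truly null, the first true null that Holm could reject comes no later than step m−m0+1. Its p-value must then be ≤ α/m0. The chance of that is at most m0·α/m0 = α under any dependence.
- At step 1 the two thresholds are both α/m, so the chance of at least one rejection is identical.

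**4. Size of the gain.** Assumptions that are not in the article: about 26 assessed per arm (32 × 0.8 = 25.6), equicorrelated normal test statistics with correlation 0.4, two-sided family-wise 5%, and effect d in SD units. The noncentrality is d·√(26/2), which is 0.8 × 3.606 = 2.88 or 0.5 × 3.606 = 1.80. Simulation used 100,000 runs per row; repeat runs differ by 0.1 to 0.2 points.

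| Tests | Real effects | d | Bonferroni | Holm | Gain (points) |
|---|---|---|---|---|---|
| 12 | 1 | 0.8 | 50.7% | 50.7% | 0.0 |
| 12 | 2 | 0.8 | 50.8% | 51.4% | 0.6 |
| 22 | 2 | 0.8 | 43.4% | 43.6% | 0.3 |
| 22 | 11 | 0.8 | 43.4% | 46.5% | 3.1 |
| 22 | 22 | 0.8 | 43.3% | 53.9% | 10.6 |
| 22 | 11 | 0.5 | 10.6% | 11.2% | 0.6 |
| 22 | 22 | 0.5 | 10.6% | 12.4% | 1.9 |
| 2 | 2 | 0.8 | 74.1% | 79.3% | 5.2 |

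Power is per real effect. For m = 2 with one real effect at 0.8 SD the gain is at most 0.2 points. No Bonferroni rejection was lost under Holm in any run. In the rows with true nulls, and under the global null for 12 and 22 tests, the family-wise error stayed at or below about 4.1%.

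**5. Sensitivity.** A second set of simulations allowed for the efficiency of the rank test (0.955). It used 25 or 32 per arm, 2 to 22 tests, d of 0.5 to 1.0 and correlation 0 or 0.5. Gains were 0.1 to 4.2 points with half the effects real and 0.5 to 15.8 points with all real. With 25 per arm, 12 tests, d = 0.8 and correlation 0.5, power went from 46.0% to 49.2% (half real) and from 46.1% to 56.9% (all real).

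**The case against.** The strongest reply is that nothing here is wrong. Bonferroni is valid, chosen in advance and conservative. It applies only if rank tests replace ANOVA, and only to secondary outcomes. It also gives simple simultaneous confidence intervals, which Holm does not. All of that stands, and it limits the weight of the point. It does not remove it, because as a testing rule Holm is never worse.

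The second reply concerns size, and it also stands. The gains of 10 to 11 points need every test in the family to carry a 0.8 SD effect, which is large and not given in the article. The family of 22 is an upper bound. A correction over the two deltas of one scale fits the wording equally well.

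A reader might also infer that Bonferroni hides a cognitive harm of the longer course, or sinks the attention hypothesis. The documents do not support this. The Objectives section expects cognitive side effects to be similar in the two arms apart from attention. That means about two real effects among the 12 cognitive tests, both on the D2, and a gain of 0.6 points at 0.8 SD (0.2 points at 0.5 SD). One isolated harm gains nothing, because Holm's first threshold equals Bonferroni's.

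**Conclusion.** The point holds as an optional efficiency gain of low weight. The article names a valid adjustment for which a uniformly no-worse alternative exists at the same family-wise error. The gain runs from nil (one real effect among 12), through about 3 points (half of 22 tests real) and about 5 points (both deltas of one scale real), to about 11 points (all real), each at 0.8 SD with 26 per arm and correlation 0.4. With 22 tests at 0.5 SD it is under 2 points. Family size, effect sizes and correlation are assumptions, so the article alone cannot fix the figure.

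It would go too far to say that real arm differences are missed for nothing. The chance of finding at least one difference is the same under both methods, and Bonferroni's simpler intervals are a real if modest advantage. The primary comparison and the 25, 32 and 64 patients are untouched.

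**What to change.** In the statistical methods section {20a}, replace the Bonferroni adjustment by a Holm step-down adjustment (two-sided, family-wise 5%), applied to the same set of Mann-Whitney tests that Bonferroni would have covered. Two-sided 5% agrees with the alpha that reproduces the sample size. Make the change before any comparison by arm is run.

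It needs no extra patients, visits or data, and adds no type 1 error. The cost is in the intervals: simultaneous confidence intervals that match Holm are harder to construct. Unadjusted intervals, labelled as such, can be shown beside the adjusted p-values, with a note that the two may occasionally disagree. If simple simultaneous intervals matter more to the sponsor than the added power, keeping Bonferroni is defensible.

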### Interim analysis {21b}

No interim analyses are planned.

### Methods for additional analysis (e.g., subgroup analyses) {20b}

This analysis will be complemented by a comparison using the logistic regression model in order to adjust for center and possible prognostic characteristics.

### Methods in analysis to handle protocol non-adherence and any statistical methods to handle missing data {20c}

Comparison of the two treatment arms will be based on the intent-to-treat principle. The maximum bias hypothesis shall be considered for non-assessed patients 3 months after the end of the treatment (patients lost to follow-up). Those patients, if in the group with the most favorable evolution, shall be considered as having not responded. On the contrary, those patients, if in the group with the most unfavorable evolution, shall be considered as responding to treatment. The aim is to reduce the gap between both to a minimum. By doing so, a robust conclusion is expected. Then, several sensitivity analyses shall be carried out: one analysis excluding patients lost to follow-up (per-protocol analysis) and another imputing the missing data by the last observed value (“last observation carried forward”).

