### Trial design {8}

This study is a prospective, multicentric, randomized, two-arm, assessor-blinded trial.

Due to the severity of the patients’ condition, it is not ethically possible to conduct sham ECT sessions, making the blinding about the short or long arm impossible to maintain in patients. In this superiority trial, patients will be randomly assigned to one of both arms with an allocation ratio of 1:1.

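### The sample size makes no allowance for the maximum-bias rule in the main analysis: the stated 80% power becomes about 76% with 5% of outcomes imputed, and about 15% if all of the planned 20% drop-out is imputed

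*Protocol article*

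**What the plan says.** **Main analysis (section {20c}).** "Comparison of the two treatment arms will be based on the intent-to-treat principle". Patients without the assessment 3 months after the end of treatment stay in the comparison under a maximum-bias rule. For the better arm: "Those patients, if in the group with the most favorable evolution, shall be considered as having not responded". In the worse arm the same patients count as responders. The purpose is stated openly: "The aim is to reduce the gap between both to a minimum". An analysis excluding patients lost to follow-up and a last-observation-carried-forward analysis come afterwards and are labelled sensitivity analyses, so the maximum-bias rule governs the main comparison. For the test, "Pearson’s chi-square test will be used" (section {20a}).

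**Sample size (section {14}).** The planned effect is given as "we postulate that the responder rates would be 61.79% in the long ECT protocol and 23.25% in the short ECT protocol". The number before any allowance for losses rests on it: "Assuming an alpha risk of 0.05 and a power of 0.80, we estimated the need to include 25 patients per group". The allowance for losses is then added on top of that figure: "To overcome an estimated 20% drop-out, the required number of patients increased to 32 patients per group". The total is 64.

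**What happens to patients who leave.** The exit criteria and section {11b} take the data of patients who withdraw consent out of the analysis. Section {18b} plans no specific retention strategy, but recommends that a patient who stops ECT go on to the next follow-up visit. The Discussion links the 20% to loss to follow-up over 15 months and concedes that data to estimate it accurately are lacking.

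**The concern.** The two sections treat the same patients differently. Dividing 25 by 0.8 is right when drop-outs leave the comparison and 25 assessed patients per arm carry the test. Under section {20c}, a patient who is lost without withdrawing consent stays in the denominator with the outcome that most reduces the difference. Such a patient does more than add no information: he or she moves the two rates towards each other.

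The consequence is a trial that can miss the effect it was designed to find, even when the planned rates and the planned drop-out are both correct. A non-significant main result could then come from the imputation rather than from the treatments, and a reader relying on the stated 80% would misjudge it.

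**Working it through.** **Inputs.** Response rates p1 = 0.6179 (long) and p2 = 0.2325 (short), alpha 0.05, power 0.80, 25 then 32 per arm, drop-out 20% (section {14}); 1:1 allocation (section {8}); Pearson chi-square (section {20a}); imputation rule (section {20c}). Assumptions: a two-sided test, which section {14} does not state but which reproduces its figure; the same missing share in both arms; missingness unrelated to response.

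**Step 1. The plan's own figure.** With pooled rate p̄ = (0.6179 + 0.2325)/2 = 0.4252,

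n = [1.96·√(2p̄(1−p̄)) + 0.842·√(p1(1−p1) + p2(1−p2))]² / (p1 − p2)²

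= (1.370 + 0.542)² / 0.1485 = 24.6, so 25 per arm. Power at 25 is 80.6%. Then 25/0.8 = 31.25, so 32. Section {14} is reproduced, with drop-outs treated as removed.

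**Step 2. Expected rates under the rule.** With imputed share d and the long arm ahead:

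- long: p1(1 − d)
- short: p2(1 − d) + d

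At d = 0.20 the long arm is 0.8 × 0.6179 = 0.494 and the short arm is 0.8 × 0.2325 + 0.2 = 0.386. The expected gap falls from 38.5 to 10.8 points.

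**Step 3. Power with 32 per arm.** The normal approximation uses the rates from step 2. The simulation draws the missing patients at random and takes the better arm from the observed data, as the rule requires.

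| Imputed share | Expected rates, long / short | Power, approximation | Power, simulation |
|---|---|---|---|
| 0% | 61.8% / 23.3% | 89.6% | 90.7% |
| 5% | 58.7% / 27.1% | 73.5% | 76% |
| 10% | 55.6% / 30.9% | 51.4% | 55% |
| 15% | 52.5% / 34.8% | 29.6% | 32% |
| 20% | 49.4% / 38.6% | 13.7% | 15.5% |

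Exact enumeration at 20% gives 15.6%. By the approximation, about 329 per arm would be needed for 80% power at 20% imputed.

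**Step 4. Part of the 20% removed, part imputed.** Patients who withdraw consent leave the analysis; the rest of the drop-outs are imputed. The splits are assumptions, because the protocol gives none.

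| Removed | Imputed | Power, simulation |
|---|---|---|
| 15% | 5% | about 64% |
| 10% | 10% | about 43% |
| 5% | 15% | about 26% |
| 0% | 20% | about 15% |

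**Step 5. Other rules at 20% missing.** Analysing observed patients only gives about 82%. Counting missing as non-response in both arms gives about 76%.

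**Step 6. One worked result.** Take 25 assessed per arm with 15/25 and 6/25 responders, close to the planned effect. The observed comparison gives p = 0.010. With 7 imputed per arm it becomes 15/32 against 6 + 7 = 13/32, and p = 0.61. The long arm would need 21/25 (84%) to reach p < 0.05.

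**The case against.** The rule is pre-specified, openly conservative, explained, and followed by two sensitivity analyses, one of which will show the result in observed patients. Which missing-data method should be primary is partly a matter of judgement. That stands, so the defect is not that the rule is conservative. It is that the sample size was calculated for a different analysis.

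Drop-out is also wider than the group that the rule covers. Patients who withdraw consent are removed, as 25/0.8 supposes. Those who only stop ECT are steered to a follow-up visit, and most patients are expected to be long-term inpatients. Both points stand, although the next visit need not be the one at 9 or 15 months. A reader might infer that the plan's power simply is 15%, or that the trial will almost certainly show no difference. The documents do not support either: 15% requires every drop-out to be imputed, and even then about 15 trials in 100 would be significant.

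A reader might also fear that the rule turns the result round. Imputation reverses the observed order of the arms in about 16% of simulated trials at 20% imputed, but in only about 1.5% at 10%. A significant result favouring the short arm occurs in about 0.2% even at 20%, so this is not a realistic danger.

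Nor is distortion of the reported rates peculiar to this rule. Non-response in both arms gives 0.8 × 61.79% = 49.4% and 0.8 × 23.25% = 18.6%, which also fall short of the assumed true rates.

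**Conclusion.** The concern holds as a mismatch between sections {14} and {20c}. The 80% belongs to a comparison that drop-outs leave; the main analysis keeps those not assessed, unless they withdrew consent, and gives them the outcome that narrows the gap. Power under the planned rates is about 76% with 5% imputed, 55% with 10%, 32% with 15% and 15% with 20%. Where the full 20% drops out and part of it is removed for consent withdrawal, the splits examined give about 64%, 43% and 26%. All of these are below 80%, so the conclusion does not depend on the extreme case.

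The figures rest on a two-sided test, 32 per arm and missingness unrelated to response. Equal drop-out matters little: by the normal approximation, unequal shares averaging 20% and all imputed (30%/10%, 25%/15% and 15%/25% in long/short) give 17.2%, 15.3% and 12.3%. The share that will actually be imputed is unknown, so a range is the fair statement.

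**What to change.** Before unblinding, change section {20c} so that the main analysis uses one missing-data rule applied alike in both arms. Two options are non-response for missing in both arms (about 76% power at 20% missing) and multiple imputation of PANSS by arm from all visits. Keep the maximum-bias rule as the extreme end of a sensitivity (tipping-point) analysis.

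If the sponsor prefers to keep the present rule as the main analysis, section {14} should replace the single 80% with a range over the imputed share, from about 76% at 5% to about 15% at 20%. It should also say how much of the 20% is expected to be consent withdrawal and how much missing assessment.

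The cost is one paragraph in the protocol and the analysis plan, with no extra patients or visits. The downside is a less conservative main result, which the retained sensitivity analysis covers.

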**Methods:**

Sixty-four patients with schizophrenia with persistent psychotic symptoms despite clozapine treatment will be enrolled in a prospective multicentric assessor-blinded randomized controlled trial. Patients will be randomly assigned to the short or the long protocol. The main outcome is the response rate assessed by the Positive and Negative Symptoms Scale (PANSS) 3 months after the end of the treatment in patients following the long protocol compared to those following the short protocol. The response was defined as a 30% reduction on the PANSS baseline. Clinical assessments (PANSS, BPRS, HAMD-21, YMRS, CGI, GAF, Modified Overt Aggression Scale (MOAS), and Subjective Scale to Investigate Cognition in Schizophrenia (SSTICS)) and plasma clozapine concentration will be performed at baseline and at 2, 4, 6, 9, 12, and 15 months. Neuropsychological measures (MMSE, RL/RI-16, Doors test, D2 Test of Attention, Copy of the Rey-Osterrieth complex figure) will be performed at baseline and at 6 and 15 months.

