##### Short ECT protocol

The short ECT protocol is a standard protocol to treat URS patients, inspired by the continuation protocols commonly used in depression [8]. However, it is limited by a relatively high relapse rate. In this protocol, 20 sessions of ECT will be administered in 6 months with the following schedule: twice a week for 6 weeks and then once a week for 4 weeks. Afterwards, the patients will have ECT sessions every 3 weeks for 6 weeks and then each month for 2 months.

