### Outcomes {12}

#### Main outcome

The main outcome is the response rate assessed by the Positive and Negative Symptoms Scale (PANSS) 3 months after the end of the treatment in patients following the long protocol (i.e., at 15 months) compared to those following the short protocol (i.e., at 9 months), the response being defined as a 30% reduction on the PANSS [12].

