### Plans to promote participant retention and complete follow-up {18b}

No specific strategy is planned to promote participant retention. However, resistant schizophrenic patients are mostly long-term hospitalized patients because of their serious illness. Being hospitalized can guarantee adherence to care. As far as possible, if the patient wishes to stop ECT sessions, it is recommended to proceed to the next follow-up visit in order to have the most concomitant data of the end of the ECT.

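### The two sensitivity analyses give the primary result only limited support: LOCF ignores relapse after ECT, with bias of either sign, and the per-protocol analysis is a complete-case analysis

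*Protocol article*

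**What the plan says.** All references are to the protocol article.

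- **Main outcome:** PANSS response is assessed "3 months after the end of the treatment in patients following the long protocol (i.e., at 15 months", and "compared to those following the short protocol (i.e., at 9 months".
- **Abstract, Methods:** the clinical scales, PANSS included, "will be performed at baseline and at 2, 4, 6, 9, 12, and 15 months".
- **Short and Long ECT protocol:** in the short arm "20 sessions of ECT will be administered in 6 months"; the long arm has 40 sessions over 12 months.
- **Section {20c}:** the primary analysis is intention-to-treat. Non-assessed patients count as non-responders in the better arm and as responders in the worse arm. Two sensitivity analyses follow: "one analysis excluding patients lost to follow-up (per-protocol analysis", and "another imputing the missing data by the last observed value".
- **Section {18b}:** a patient who wants to stop ECT should go on to the next follow-up visit "in order to have the most concomitant data of the end of the ECT".
- **Sample size {14}:** "the relapse following ECT cessation is very high". A 62.5% relapse rate turns a 62% response rate into the 23.25% planned for the short arm.

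**The concern.** LOCF is used for an endpoint that is meant to be measured off treatment. If the last available score was taken on ECT or as ECT ended, carrying it forward assumes that the response persists once ECT stops. The trial exists because that is doubted, and its sample size depends on response being lost. The conflict is inside this protocol, so it goes beyond a general dislike of LOCF.

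The second issue is a label. A per-protocol set should be selected on adherence to the allocated treatment. The stated set is selected only on being assessed. A patient who missed many sessions but attended the endpoint visit stays in. The section is headed as dealing with non-adherence, yet no analysis in it uses adherence.

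The primary rule is severe, so readers may plausibly turn to these two analyses to judge the result.

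**Working it through.** **1. The plan's own figure.** Inputs from Sample size {14}: 61.79% and 23.25%, alpha 0.05, power 0.80. Two sides and no continuity correction are assumed, as neither is stated. The mean rate is (0.6179 + 0.2325)/2 = 0.4252.

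n = [1.96·√(2·0.4252·0.5748) + 0.8416·√(0.6179·0.3821 + 0.2325·0.7675)]² / 0.3854² = 24.6, so 25 per arm. Then 25/0.8 = 31.25, so 32 per arm and 64 in total. The stated size reproduces.

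**2. What LOCF carries.**

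| | Short | Long |
|---|---|---|
| ECT course ends (month) | 6 | 12 |
| Last PANSS visit before the endpoint | 6 | 12 |
| Endpoint | 9 | 15 |

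No visit falls between the end of ECT and the endpoint in either arm. A patient missing at the endpoint normally carries an on-ECT or end-of-ECT score, or baseline if they left before month 2.

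**3. Planning rates true, 20% missing in each arm.** Assumed: equal loss, unrelated to outcome. Expected rate in an arm = 0.8 × endpoint rate + 0.2 × value given to the missing.

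| Analysis | Long | Short | Difference (points) | Power |
|---|---|---|---|---|
| Complete-case (25.6 per arm) | 61.79% | 23.25% | 38.5 | 0.82 |
| LOCF, 61.79% carried in both arms | 61.79% | 0.8·23.25 + 0.2·61.79 = 30.96% | 30.8 | 0.71 (exact 0.74) |
| Maximum-bias primary | 0.8·61.79 = 49.4% | 0.8·23.25 + 20 = 38.6% | 10.8 | 0.14 (exact 0.16) |

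The LOCF error falls in the short arm and works against the long arm. Any carried rate common to both arms gives the same 0.8 × 38.54 = 30.8 points (checked from 0 to 80%).

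**4. No true effect, 23.25% off ECT in both arms.** False difference = (long loss − short loss) × (carried rate − 0.2325).

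*Constant drop-out hazard* h = −ln(1 − D)/15, with D the loss by month 15. Loss while on ECT is 1 − exp(−12h) in the long arm and 1 − exp(−6h) in the short arm.

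| D | Long | Short | Carried 61.79% | Carried 30% | Carried 10% |
|---|---|---|---|---|---|
| 20% | 16.3% | 8.5% | +3.0 | +0.5 | −1.0 |
| 30% | 24.8% | 13.3% | +4.4 | +0.8 | −1.5 |

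Counting everyone missing at the endpoint (for D = 20%, 20% long and 12.5% short) gives +2.9 points, and +4.1 for D = 30%, so the result is stable. With 32 per arm, 3.0 and 4.4 points are about 1.0 and 1.4 patients. The exact rejection rate of the chi-square test is 0.060 and 0.069, against 0.051 without bias.

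*Unequal loss, 61.79% carried.* At 30% long and 10% short: 0.20 × 38.54 = +7.7 points, rejection rate 0.10. At 10% long and 30% short: −7.7 points, rejection rate 0.10. At 20% in both arms: no bias.

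**5. The per-protocol set.** The only stated exclusion is loss to follow-up. No condition is set on sessions received, clozapine concentration or prohibited treatment.

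**The case against.** A reader might infer that LOCF favours the long arm because those patients spend longer on ECT. The documents do not support that as a general statement. The 3 to 4 points arise only if long-arm leavers are given the short-arm off-ECT rate. Sample size {14} puts the long arm at 61.79% at the endpoint itself, and on those rates the error lies in the short arm. Section {11b} also lists an exit reason that exists only in the short arm, the wish for more ECT, which could raise loss on that side. Worsening and adverse effects are exit reasons too, so carried scores may be far below 61.79%. All of this stands, and it removes any fixed direction.

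A reader might also infer that these analyses cannot support the primary result at all. That goes too far. The primary already imputes against the observed difference, and a complete-case analysis is a legitimate, if weak, companion to it, valid when missingness is unrelated to outcome.

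On the label, it can be said that the same phrase states what is done, that investigator-decided exits make the assessed patients partly adherence-selected, and that detailed set definitions belong in an analysis plan not shown here. The first two soften the point. The third does not answer it: the article does give a definition, and it does not match the name.

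**Conclusion.** Both facts hold. LOCF fills an off-ECT endpoint with a score that normally precedes any relapse after ECT, against the protocol's own 62.5%. The per-protocol analysis is a complete-case analysis. The two analyses therefore give limited support: on the planning rates with equal loss both are less conservative than the primary (38.5 and 30.8 points against 10.8), and neither addresses post-ECT relapse or adherence.

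The LOCF bias can take either sign. It is a loss of 7.7 points for the long arm under the planning rates with 20% missing per arm. With no true effect it is a false long-arm gain of about 3 to 4 points under a constant hazard, and 7.7 points at 30% versus 10% loss. It shrinks or reverses with a lower carried rate or more short-arm loss. These sizes rest on assumed drop-out patterns and carried response rates; the documents give only the 20% overall drop-out and the planning rates. An unpredictable sign is itself a weakness in a sensitivity analysis.

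**What to change.** - Rename the exclusion analysis complete-case. Use per-protocol only for a set defined by ECT sessions received, if one is wanted.
- Replace LOCF with multiple imputation, within arm, of the PANSS three months after ECT, from baseline and all observed visits, and derive response from the imputed score. Add a tipping-point (delta) variation that makes the imputed scores worse to represent relapse after ECT. An on/off-ECT indicator would add little, since ECT status is almost fixed by visit within each arm.
- Add an analysis that counts all non-assessed patients in both arms as non-responders.

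The cost is analysis wording and a little programming, with no new data. The downside is that imputation models will be imprecise at about 32 patients per arm and also rest on an untestable assumption. The delta variation is there to show how much the result depends on it.
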